### Statistical analysis

All participant data will be entered into Epidata Manager or RedCap software to facilitate electronic capture of the data. After data cleaning using programmed logic checks and assessment for logic accuracy and consistence, the final database will be locked. The data will be analyzed using the Statistical Package for Social Scientists (SPSS) version 26.0. A table of baseline

characteristics will be drawn with continuous and categorical variables between the intervention and control arm compared using T-test, linear regression, Fisher's exact and Chi-Square tests respectively. A p-value of less than will be considered statistically significant. The individuals will be compared on the outcomes shown in table 2 above of this sub-study following an Intention to treat analysis (ITT) approach. The ITT population will be defined as all randomized patients with data for the outcomes. However, per protocol analysis will also be carried out and results compared with the ITT. The results will be reported following the CONSORT 2010 guidelines.

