## Operational Definitions

**ACT:** Third wave cognitive behavioral therapy that combines mindfulness, acceptance, values clarification and behavioral goal setting to improve wellbeing through a process called psychological flexibility. ACT fosters psychological flexibility through six sub-processes; experiential acceptance, contact with the present moment, defusion, self-as-context, values, and committed action .

**DNA-v:** An evidence-based model that promotes psychological strength, values consistent living, vitality, and success. It is designed to help young people cope with challenges, stress, and change. DNA-V is a combination of Acceptance and Commitment Therapy (ACT) and positive psychology, and is underpinned by contextual behavioral science .

**Adolescent:** The World Health Organization (WHO) defines an adolescent as someone within the age range of 10 years – 19 years. For this particular study, we shall focus on older adolescents 15 – 19 years of age .

**Psychological Flexibility:** Contacting the present moment fully as a conscious human being, and based on what the situation affords, changing or persisting in behavior in the service of chosen values.

**Cognitive fusion:** Process that involves attaching a thought to an experience. This results in entanglement and believing thoughts as if they are real. The mindfulness and acceptance intervention is targeted at creating a detachment between thoughts and experiences .

**Mindfulness:** Being intensely aware of what you're sensing and feeling in the moment, without interpretation or judgment .

**Acceptability:** Exploring perceptions and experiences of providers (HCPs) and users (adolescents) regarding the intervention. Exploration will be done following the 7 domains of the theoretical framework for acceptability (TFA; affective attitude, burden, perceived effectiveness, ethicality, intervention coherence, opportunity cost and self-efficacy . Narratives from providers and users will determine if the intervention is acceptable.

**Feasibility:** Degree of convenience for use. If 70% of participants contacted consent/assent to participate, are retained in study for 6 months, adhere to the protocol, complete at least 4 out of 6 sessions and assignments, and recruitment happens in one month as planned, then intervention will be considered feasible .

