### Hypothesis.

- (i) Participants receiving the ACT-DNA-v intervention will report a significant reduction in depression, anxiety & stigma at post-intervention assessment as compared to participants in the control group.

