Relatedly, a study on ACT for youth with neurofibromatosis Type 1 (NF1) and chronic pain, which also included their parents assessed the efficacy and feasibility of a 2-day ACT workshop for this cohort of people. Some of their secondary aims looked to find any changes in pain intensity, pain-related anxiety depression and pain acceptance. The intervention had 3 -5 patients per group, with a 2-hour session over 2 days with a " booster" session after a month and then completed a 3-month post-intervention follow-up questionnaire. The study found that pain interference and pain intensity were significantly lower post-intervention. Parents reported their children's pain acceptance to have increased. Patient satisfaction for the intervention was 3.9/5 and parental satisfaction was 4.6/5. Both patients and parents expressed that it taught them great strategies for dealing with pain.

Livheim et al. compared ACT to TAU (school counselling), for adolescents with depression and stress in Australia and Sweden. The study had a good retention rate (66 enrolled and 51 assessed post-intervention). They found greater improvement in depression and stress and also noted a decrease in anxiety. Acceptability was high in both sites, with 91% of participants giving exclusively positive feedback, saying that they would recommend this to a friend and found it valuable. They concluded that ACT interventions can be especially helpful for adolescents. It is also important to note that ACT-based therapies are values-driven, thus interventions that promote values among adolescents can have significant outcomes. Bryan et al. note that adolescents will usually do what their peers are doing, in the hopes of maintaining the same values. So harnessing values in peers can help others get on board, this is where a value-based intervention can be useful . Some other ways ACT can be useful for adolescents include; dealing with rebellion, handling negative social comparisons, developing career aspirations and

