#### Outcome measures.

Measured clinical primary outcomes will include Experiences of depression, anxiety and internalized stigma. Then process outcomes will include; Psychological flexibility (cognitive fusion and experiential avoidance) to test the mechanism of change and secondary outcomes will be; self-reported adherence and viral load (obtained from clinical charts).

Table 2; Showing study measures, analysis and outcomes.

| Objective                                                             | Variables                                                                                                                                      | Informant | Measures                                                                                                                                                                                                                                                                                                                                                                                                                                                      | Analysis & Outcomes                                                                                                                                                                                                                                                                                                                                                                             |

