| To examine the impact of ACT-DNA-v on reducing proximal psychosocial barriers to medication adherence (depression, anxiety and stigma) among ALWHA | Depression
Anxiety
Internalized stigma            | ALWHA | Qualitative surveys using standardized data collection instruments.
* Reynolds Adolescents depression scale (RADS-2)
* Social anxiety scale for adolescents-short form (SA-A-SF).
* Internalized AIDS-related stigma scale (IARSS-6). | 
Analysis
We shall run a T-test, linear regression, and Fisher's exact and Chi-square tests respectively to obtain mean differences between groups.
 
Outcomes we hypothesize that;
*The average means score of ALWHA in the intervention arm should be in the mild depression range of the BDI-ii (14-19) at post-intervention and follow-up, adjusting for baseline compared to the mean score of ALWHA in the control group.
* The average mean score of ALWHA in the intervention arm should be below the cutoff score of 40.5 as measured by the SHAI at post-intervention and follow-up.
* After dichotomizing the IARSS-6 at median value (0-2 & 3-6), average mean scores of participants in the intervention arm should fall in category1 (0-2) at post-intervention and follow-up.
 |

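### The population labelled ITT requires an observed outcome, so it is an available-case (modified ITT) set and no planned analysis covers everyone randomised

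*Protocol*

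**What the plan says.** The protocol's Statistical analysis section says that participants will be compared on the Table 2 outcomes "following an Intention to treat analysis (ITT) approach". It then defines the set: "The ITT population will be defined as all randomized patients with data for the outcomes". The only other analysis set is per protocol: "per protocol analysis will also be carried out and results compared with the ITT".

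The outcomes concerned are the main ones: "Measured clinical primary outcomes will include Experiences of depression, anxiety and internalized stigma". The hypothesis places the comparison "at post-intervention assessment as compared to participants in the control group". Table 2 gives the methods: "We shall run a T-test, linear regression, and Fisher's exact and Chi-square tests respectively to obtain mean differences between groups". It mentions adjustment for baseline for the depression scale (BDI-II) and the psychological inflexibility scale (AFQ-Y8), but not for the anxiety (SHAI) or stigma (IARSS) scales.

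Missing data appear only as a feasibility measure, under Data collection and measures and in Table 2. The sample size section allows for 10% loss to follow-up. The feasibility definition under Operational Definitions applies a 70% mark to participants who "are retained in study for 6 months, adhere to the protocol, complete at least 4 out of 6 sessions and assignments".

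**The concern.** Under intention-to-treat, randomisation alone decides who belongs to the analysis set. Here membership also depends on whether an outcome was recorded, which happens after randomisation and may be related to arm and to the outcome. The stated rule therefore contradicts the approach announced just before it. The planned tests and regressions use observed outcomes only, so nothing else in the plan brings the missing participants back. The comparison of ITT with per protocol would set one observed-outcome set against what will normally be a smaller one.

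The protocol gives reasons to expect missingness that is not random. Its literature review says that adolescents experiencing stigma often abandon care, and internalised stigma is a primary outcome. It also reports that some people with HIV found the emotional content of ACT overwhelming, which could act only in the intervention arm. The trial is open label, and only one arm attends sessions and receives the incentives tied to them. These pressures need not pull the same way, so the direction of any net bias cannot be known beforehand. Readers who see ITT will assume that all 116 participants are in the comparison.

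**Working it through.** **Inputs from the sample size section.** Difference 4.09, SD 5.13, two-sided alpha 0.05, power 80%, design effect 2.0, loss 10%. The illustration is in SD units because these figures come from RADS-2, while the Study instruments section lists BDI-II.

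**The plan's own figure.**
- n per group = 2 × (1.96 + 0.84)² × 5.13² / 4.09² = 24.7. The protocol prints 25.1 and uses 26; the gap is about one participant and plays no part here.
- 26 × 2.0 = 52; 52 / 0.90 = 57.8, rounded up to 58 per group, 116 in total. Reproduced.
- Planned effect: 4.09 / 5.13 = 0.80 SD.

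**Who leaves the set.**
- 10% loss: 0.10 × 116 = 11.6, about 12 excluded and 104 analysed.
- 30% loss, the complement of the 70% feasibility mark: 0.30 × 116 = 34.8, about 35 excluded and 81 analysed.
- For context, the literature review says of the pilot that supplied the effect size: "The study had a good retention rate (66 enrolled and 51 assessed post-intervention". That is 15 / 66 = 23% not assessed.

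**Power is not the main issue.** With m analysed per arm and design effect 2, power ≈ Φ(√(m/4) × 0.797 − 1.96).
- 10% loss, m = 52.2: Φ(0.92) = 82%.
- 30% loss, m = 40.6: Φ(0.58) = 72%.

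The planned loss is already in the sample size, so at 10% the question is bias.

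**Bias of the observed-outcome comparison.** In each arm let p be the fraction missing and g the gap in SD between drop-outs and completers (positive means worse). The mean of all randomised in that arm is the completer mean plus p × g, so

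bias = p(intervention) × g(intervention) − p(control) × g(control),

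with a positive value favouring the intervention. The documents give no g; the range 0.25 to 1 SD is an assumption.

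| Scenario | Bias (SD) | Share of 0.80 SD |
|---|---|---|
| Missingness unrelated to outcome given arm (g = 0) | 0 | 0% |
| Equal loss and equal gap in both arms | 0 | 0% |
| 10% loss in each arm, gap in the intervention arm only | 0.025 to 0.10 | 3% to 13%, favouring the intervention |
| 10% loss in each arm, gap in the control arm only | 0.025 to 0.10 | 3% to 13%, against the intervention |
| 15% v 5% loss (intervention v control), same gap in both arms | 0.025 to 0.10 | 3% to 13%, favouring the intervention |
| 30% loss in each arm, gap in the intervention arm only | 0.075 to 0.30 | 9% to 38%, favouring the intervention |

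**The case against.** Several points on the other side stand.

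- **The set is not per protocol.** Anyone randomised and assessed is included, even with no sessions attended, and nobody changes arm. Missing sessions is not the same as missing an assessment. A reader might infer that the protection of randomisation is lost altogether; the documents support only that it is weakened to the extent that outcomes are missing.
- **Not everyone lost to follow-up is dropped from everything.** On the natural reading, someone lost after the post-intervention visit still counts there, and that is the time point of the hypothesis. The plural wording could also mean that all outcomes are required, which would exclude more people; the text does not settle it.
- **The direction is open.** A reader might infer that the result will favour ACT-DNA-v. Nothing in the protocol establishes this: if worse-off controls leave, the bias runs the other way.
- **The 70% is a pass mark, not a forecast.** It concerns retention at six months, whereas the schedule places assessments in months 3, 6 and 11. The 35 of 116 is therefore what the plan would tolerate, not what it expects.
- **A more elaborate model does not cure this by itself.** A participant with only a baseline score adds almost nothing to the treatment contrast in a mixed model. If missingness depends only on arm and baseline, baseline-adjusted regression on observed outcomes is also valid.
- **The definition is stated openly,** and the plan commits to reporting retention, missing data and reasons for withdrawal under CONSORT. The aim is preliminary effectiveness.

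Missing-data methods commonly sit in an analysis plan that is not shown, and their absence here is not the point. The definition is: an analysis plan that kept all randomised participants would contradict the protocol as written.

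**Conclusion.** The point holds as a contradiction between the announced approach and the stated population. The set is available-case by allocated arm, and no planned analysis covers everyone randomised.

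The expected size is modest at the planned loss: about 12 of 116 excluded and, if a gap of 0.25 to 1 SD exists in one arm only, a bias of 3% to 13% of the planned effect in either direction. It grows in proportion to loss. These figures illustrate scale and do not predict it, because the gap is assumed and bias vanishes under the two conditions shown in the working. The correction still matters because the set underlies all three primary comparisons and the trial is open label, so the rule should be settled before outcomes are seen.

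**What to change.** 1. Define the ITT population as all randomised participants, analysed in the arm allocated.
2. Rename the present definition the available-case (modified ITT) population, say whether it applies per outcome and assessment, and keep it as a supporting analysis.
3. Make the primary comparison baseline-adjusted for every scale, including anxiety and stigma. Use either baseline-adjusted regression with multiple imputation, or a repeated-measures mixed model using all post-baseline scores.
4. Add a sensitivity analysis that shifts the imputed values for missing outcomes in each arm separately and in both directions, for example over 0.25 to 1 SD of each scale. This step carries the weight, because neither primary model removes bias when missingness depends on the unseen outcome.

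The cost is revised wording, a little more analysis work and possibly slightly wider intervals. No new data are needed and the sample size stays at 116.

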## Schedule of activities

|                                                               | 1 st Month | 2 nd Month | 3 rd month | 4 th month | 5 th month | 6 th month | 7 th month | 8 th month | 9 th month | 10 th month | 11 th month |
|---------------------------------------------------------------|-----------------------|-----------------------|-----------------------|-----------------------|-----------------------|-----------------------|-----------------------|-----------------------|-----------------------|------------------------|------------------------|
| INTERVENTION AND CONTROL GOUPS                         |                       |                       |                       |                       |                       |                       |                       |                       |                       |                        |                        |
| Eligibility Screen                                            | x                     |                       |                       |                       |                       |                       |                       |                       |                       |                        |                        |
| Informed Consent                                              | x                     |                       |                       |                       |                       |                       |                       |                       |                       |                        |                        |
| Adapting and Exploring acceptability of the adapted ACT-DNA-V | x                     | X                     |                       |                       |                       |                       |                       |                       |                       |                        |                        |
| Recruiting for Quantitative study                             |                       |                       | X                     |                       |                       |                       |                       |                       |                       |                        |                        |
| Baseline assessment                                           |                       |                       | X                     |                       |                       |                       |                       |                       |                       |                        |                        |
| Post intervention assessment                                  |                       |                       |                       |                       |                       | X                     |                       |                       |                       |                        |                        |
| Assessment at 4 months Follow                                 |                       |                       |                       |                       |                       |                       |                       |                       |                       |                        | x                      |
| INTERVENTION GROUP                                     |                       |                       |                       |                       |                       |                       |                       |                       |                       |                        |                        |
| Mindfulness and ACT                                           |                       |                       |                       | X                     |                       |                       |                       |                       |                       |                        |                        |
| The noticer-Increasing noticing skill                         |                       |                       |                       | x                     |                       |                       |                       |                       |                       |                        |                        |
| The advisor-Normalizing experiences                           |                       |                       |                       | X                     |                       |                       |                       |                       |                       |                        |                        |
| Discoverer-Building resilience                                |                       |                       |                       |                       | X                     |                       |                       |                       |                       |                        |                        |
| Values clarification-connecting to values                     |                       |                       |                       |                       | X                     |                       |                       |                       |                       |                        |                        |
| Connecting the disc-bringing it to life                       |                       |                       |                       |                       | X                     |                       |                       |                       |                       |                        |                        |
| CONTROL GROUP                                          |                       |                       |                       |                       |                       |                       |                       |                       |                       |                        |                        |
| Standard Care                                                 |                       |                       |                       | x                     | x                     |                       |                       |                       |                       |                        |                        |

## Intervention fidelity

To ensure that delivery of the intervention adheres to the underlying theoretical premises and the protocol, sessions will be audiotaped and reviewed by two independent raters (ACT experts) to determine if all critical components are delivered. The aim will be to achieve a fidelity rating of at least 85% for all sessions.

